#### Data management

4.8.5

Data will be collected using standardized paper-based case record forms and validated outcome assessment instruments completed by participants during scheduled visits. The collected data will subsequently be entered into a password-protected Microsoft Excel spreadsheet maintained on a secure institutional computer. The Excel file will be stored within an encrypted folder with restricted user access, limited to the Principal Investigator and the designated Co-Investigator. A separate master linkage file containing participant identifiers will be maintained independently from the analytical dataset in a secured location accessible only to these investigators. The Principal Investigator will oversee all data management procedures and periodically verify the completeness and accuracy of entries. The Co-Investigator will be responsible for entering outcome scores, follow-up notes, and documented observations into the Excel sheet while maintaining blinding where applicable. All participant data will be coded using unique study identification numbers. Only validated instrument scores and documented clinical observations will be included in the final analytical dataset. The Statistician, who remains blinded to group allocation, will receive an anonymized dataset exported from the Excel file for analysis according to the pre-specified statistical analysis plan. Regular backups will be maintained on secure institutional servers to ensure data integrity and prevent data loss. Role-based access restrictions will be implemented throughout the study to maintain confidentiality.

### Exploratory statistical analysis plan

4.9

Baseline demographic and clinical characteristics; including age, duration of insomnia, comorbidities, and medication history will be summarized separately for the intervention and control groups. Continuous variables will be reported as mean ± standard deviation (SD) for normally distributed data or as median with interquartile range (IQR) for non-normally distributed data. Categorical variables will be presented as frequencies and percentages. Baseline group comparisons will be explored using Independent *t*-tests or Mann–Whitney U tests for continuous variables and Chi-square or Fisher’s exact tests for categorical variables, as appropriate. These comparisons are descriptive and intended to characterize the sample rather than to establish statistical equivalence. The exploratory primary and secondary outcomes are defined in detail in the Outcome Measures section. Analyses are estimation-focused and hypothesis-generating in nature.

#### Exploratory primary outcome analysis (week 4)

4.9.1

Change from baseline to Week 4 in ISI score will be summarized for each group. Between-group differences in mean change will be estimated using Independent *t*-tests for normally distributed data or Mann–Whitney U tests for non-normally distributed data. Effect sizes with 95% confidence intervals will be reported. *p*-values will be presented for descriptive purposes and interpreted cautiously within the exploratory framework.

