### Exploratory primary outcome

4.1

(Assessed at Week 4—end of intervention phase).

Insomnia Severity Index (ISI) — change from baseline to Week 4.

Measurement variable: ISI total score (range 0–28).Analysis metric: Mean change from baseline to Week 4; between-group mean difference with 95% confidence interval.

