### Sample size

4.5

This study is designed as an exploratory randomized controlled trial intended to estimate preliminary between-group differences and assess feasibility parameters rather than to establish confirmatory superiority.

The sample size was estimated using the standard formula for comparison of two independent means:

$$n=\frac{2s_{p}^{2}{\left(Z_{1-\alpha /2}+Z_{1-\beta }\right)}^{2}}{{\left(\mu_{1}\mu_{2}\right)}^{2}}$$

where 
$s_{p}$
 represents the pooled standard deviation, 
$\mu_{1}-\mu_{2}$
 represents the expected mean difference between groups, 
$Z_{1-\alpha /2}$
, 
$Z_{1-\beta }$
 correspond to conventional planning parameters.

The expected post-intervention ISI mean in the intervention group (6.9) was informed by pilot observations in perimenopausal women receiving *Siro-pichu* and *Padabhyanga* with *Ksirabala Taila*. The expected post-intervention ISI mean in the control group (10.9) was derived from Ayabe et al. (49), a multicenter randomized controlled trial evaluating CBT-I in adults with pharmacotherapy-resistant insomnia. Although the Ayabe et al. study included both sexes, the majority of participants were women with a mean age of 52 years, supporting its relevance to the present perimenopausal population (49, 50). The anticipated mean difference between groups was therefore approximately 4 points on the ISI scale. A pooled standard deviation of 4.3 was derived from pilot data. Using a two-sided alpha of 0.05 and 90% power as conservative planning parameters with a 1:1 allocation ratio, the required sample size was estimated at approximately 26 participants per group. Allowing for an anticipated attrition rate of 15%, the final planned sample size was set at 31 participants per arm (total *N* = 62). This calculation was applied as a pragmatic planning tool to avoid underestimation of participant numbers and to permit preliminary effect-size estimation. The study is not powered for confirmatory hypothesis testing, and findings will be interpreted within an exploratory, hypothesis-generating.

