#### Sequence generation

4.7.1

The random allocation sequence will be generated prior to participant enrollment by an independent statistician using R statistical software (version 4.1.5). Block randomization with a fixed block size of 4 will be used to ensure balanced allocation between study arms throughout recruitment. The allocation ratio will be 1:1 (Intervention Group: Control Group). No stratification factors will be applied. The statistician will not be involved in recruitment, intervention delivery, or outcome assessment.

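### The Mann–Whitney branch of the primary analysis does not estimate the promised mean difference, and baseline ISI goes unused; prespecified ANCOVA would cure the first and usually narrow the interval

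*Protocol article*

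**What the plan says.** Section 4.1 of the protocol article gives the analysis metric for the primary outcome, the ISI at Week 4, as "Mean change from baseline to Week 4; between-group mean difference with 95% confidence interval". No condition on the distribution is attached.

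Section 4.9.1 says how that difference is to be estimated: independent t "tests for normally distributed data or Mann–Whitney U tests for non-normally distributed data", applied to change from baseline. It adds that effect sizes with 95% confidence intervals will be reported and that p-values are descriptive. It gives no criterion for normality and names no baseline covariate. Section 4.9 describes the analyses as focused on estimation and refers to the outcome section for definitions.

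Section 4.5 plans on post-intervention scores. "The expected post-intervention ISI mean in the intervention group (6.9) was informed by pilot observations"; "The expected post-intervention ISI mean in the control group (10.9) was derived from" a published trial of CBT-I; "The anticipated mean difference between groups was therefore approximately 4 points on the ISI scale". For the spread it says only: "A pooled standard deviation of 4.3 was derived from pilot data". It does not say whether this is the SD of Week 4 scores or of change.

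Baseline ISI is measured in all participants before randomisation (section 4.3 and Table 1). On the allocation list, section 4.7.1 says "No stratification factors will be applied".

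**The concern.** Two separate things are at issue.

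The first is what gets estimated. A Mann–Whitney test compares ranks. The estimate that goes with it is a location shift or a probability of superiority, not a difference in means. If the data are judged non-normal, section 4.9.1 as worded puts a different quantity in place of the one fixed in section 4.1. The reader cannot know beforehand which will appear.

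The second is precision. Baseline ISI is available at no cost and is likely to predict Week 4 ISI. A change score subtracts the whole baseline value whatever its true relation to the Week 4 value. When that relation is weak, subtraction adds noise. Regression on baseline estimates the relation and uses it.

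Both matter because the article says its main product is an effect estimate to plan a later trial, and section 6 says the sample is meant to give that estimate with reasonable precision.

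**Working it through.** **The plan's own figure.** Inputs from section 4.5: difference 10.9 − 6.9 = 4, SD 4.3, and "Using a two-sided alpha of 0.05 and 90% power as conservative planning parameters with a 1:1 allocation ratio".

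- Normal approximation: n = 2 × 4.3² × (1.960 + 1.282)² / 4² = 24.3, so 25 per arm.
- With the t distribution: 25.3, so 26 per arm, as stated.
- Attrition: 26 / 0.85 = 30.6, so 31 per arm and N = 62, as stated.
- Power at 26 per arm with SD 4.3, from the noncentral t: 90.8%.

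The sample size reproduces.

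**Assumptions for the comparison.** The article gives neither the baseline SD (s0) nor the baseline–Week 4 correlation (ρ). I take the Week 4 SD as 4.3. I take s0 as 3.0–3.5, because entry is limited to ISI 8–21, and ρ as 0.2–0.7. I add s0 = 4.3 at ρ = 0.3 as an outer case.

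**Formulas.**

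- SD of change = √(s0² + 4.3² − 2 × ρ × s0 × 4.3)
- ANCOVA residual SD = 4.3 × √(1 − ρ²)
- Standard error = SD × √(2/26), so the proportional reduction in SE is 1 − (ANCOVA SD / change SD)
- Power for 4 points from the noncentral t, with 50 degrees of freedom for the t-test and 49 for ANCOVA

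Worked case, s0 = 3.5 and ρ = 0.3: SD of change = √(12.25 + 18.49 − 9.03) = √21.71 = 4.66. ANCOVA SD = 4.3 × √0.91 = 4.10. Reduction = 1 − 4.10/4.66 = 12%.

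| s0 | ρ | SD change | SD ANCOVA | SE reduction | Power, change | Power, ANCOVA | 95% CI half-width, change / ANCOVA |
|---|---|---|---|---|---|---|---|
| 3.0 | 0.2 | 4.73 | 4.21 | 11% | 85% | 92% | 2.63 / 2.35 |
| 3.0 | 0.3 | 4.44 | 4.10 | 8% | 89% | 93% | 2.48 / 2.29 |
| 3.0 | 0.5 | 3.82 | 3.72 | 2.5% | 96% | 97% | 2.13 / 2.08 |
| 3.0 | 0.7 | 3.07 | 3.07 | 0% | 99.6% | 99.6% | 1.71 / 1.71 |
| 3.5 | 0.2 | 4.97 | 4.21 | 15% | 81% | 92% | 2.77 / 2.35 |
| 3.5 | 0.3 | 4.66 | 4.10 | 12% | 86% | 93% | 2.60 / 2.29 |
| 3.5 | 0.5 | 3.96 | 3.72 | 6% | 95% | 97% | 2.21 / 2.08 |
| 3.5 | 0.6 | 3.56 | 3.44 | 3.4% | 98% | 98% | 1.98 / 1.92 |
| 4.3 | 0.3 | 5.09 | 4.10 | 19% | 79% | 93% | 2.83 / 2.29 |

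**When the change-score SD exceeds 4.3.** Setting the first formula above 4.3 gives ρ < s0 / (2 × 4.3) = s0 / 8.6. That is 0.35 at s0 = 3.0, 0.41 at 3.5 and 0.50 at 4.3. Because 26 per arm gives 90.8% at SD 4.3, power drops under 90% only a little below those thresholds: at s0 = 3.5 and ρ = 0.4 the SD is 4.32 and power still 90.5%. The ANCOVA residual SD cannot exceed 4.3 at any ρ.

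**How often the switch would operate.** The article names no normality test, so this too is an assumption. In simulated trials with near-normal underlying data (26 per arm, ISI rounded to integers, s0 = 3.5, ρ 0.3–0.5), a Shapiro test in each arm at the 5% level sent about 12–14% to Mann–Whitney. A single test on pooled residuals sent about 6%. At ρ = 0.3 and a 4-point difference, simulated power was 87.0% for the plain t-test, 86.7% for the two-stage rule and 92.5% for ANCOVA.

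**The case against.** The strongest reply is that nothing here is invalid. In a randomised trial an unadjusted t-test on change is unbiased and gives exactly the metric of section 4.1. Section 4.9.1 also promises effect sizes with 95% confidence intervals. Since section 4.1 sets the mean difference without conditions, it might be reported whichever test supplies the p-value. The first part stands in full. The second is a possible reading, but section 4.9.1 says the difference is estimated by the chosen test, and an effect size attached to a rank test is a different quantity. The wording needs to settle it.

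Some stronger conclusions are tempting but not supported:

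- **That ANCOVA matches the planning SD, or that the trial is underpowered.** Section 4.5 does not say which score the 4.3 describes. If it is the SD of change, the t-test already fits the calculation. If it is the SD of Week 4 scores, 4.3 is an upper bound for the ANCOVA SD, reached only at ρ = 0. The article also disclaims confirmatory power, so power is a secondary yardstick.
- **That chance imbalance in baseline ISI biases the result, or that unstratified randomisation is a fault.** A 1.96-SE imbalance at s0 = 3.5 is 1.96 × 3.5 × √(2/31) = 1.74 points. It would move the change-score estimate by (1 − ρ × 4.3/3.5) × 1.74, about 0.7–1.3 points for ρ from 0.5 down to 0.2. That is a roughly 1-in-20 event, and the confidence interval already allows for it.
- **That the normality rule costs power.** The simulation shows almost no loss (87.0% against 86.7%). The gap to ANCOVA comes almost wholly from the missing adjustment.

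**Conclusion.** The point holds as a defect confined to one branch, plus a free improvement. The defect: under non-normality the stated method does not estimate the mean difference with 95% CI that section 4.1 fixes, and the criterion for switching is not stated. The improvement: adjusting for baseline ISI is never less precise, apart from one degree of freedom.

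The size of the gain rests on assumed values that the article does not give. The SE falls by about 2.5–15% for baseline SD 3.0–3.5 and ρ 0.2–0.5, and by only 0–3.4% for ρ 0.6–0.7. The possible shortfall against 90% power (about 86% at baseline SD 3.5 and ρ 0.3) further requires that 4.3 be the post-intervention SD. That is the natural reading, since the planning means are post-intervention, but it is an inference.

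**What to change.** In section 4.9.1, prespecify linear regression of Week 4 ISI on arm and baseline ISI. Using change as the response gives the same treatment estimate. Report the adjusted mean difference with 95% CI whatever the distribution looks like.

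Fix the standard-error method in advance, for example robust or bootstrap for all analyses, so that one choice made from the data is not replaced by another. Keep the Mann–Whitney test as a sensitivity analysis only.

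Use the same model for ISI at Week 2 and PSQI at Week 4, each with its own baseline value. In section 4.5, state whether the SD of 4.3 refers to Week 4 scores or to change.

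The cost is an amendment of wording before analysis. No new data are needed and N need not change.

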#### Exploratory secondary outcome analysis

4.9.2

Follow-up ISI and PSQI scores beyond Week 4 will be summarized descriptively. Data will be presented as mean ± SD or median (IQR), and graphical trends over time will illustrate within-group patterns. No formal repeated measures ANOVA or confirmatory longitudinal modeling is planned. These analyses are exploratory and not adjusted for multiple comparisons. Sleep-duration categories (<6 h, 7–9 h, >9 h) will be used for descriptive summaries and exploratory subgroup analysis. No confirmatory inference will be based solely on duration categories. Adverse events will be summarized by frequency and proportion in each group. Between-group comparisons will be explored using Chi-square or Fisher’s exact tests. Severity of Dependence Scale (SDS) scores and adherence percentages will be summarized descriptively and compared between groups using appropriate parametric or non-parametric tests. Findings will be interpreted as exploratory.

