### Exploratory secondary outcomes

4.2

The following outcomes explore early response, durability of effect, sleep quality, safety, behavioral reliance, and adherence. These analyses are exploratory and descriptive in nature. No adjustment for multiple comparisons is planned.

Pittsburgh Sleep Quality Index (PSQI) — change from baseline to Week 4.

Measurement variable: PSQI global score (range 0–21).Analysis metric: Mean change from baseline to Week 4; between-group mean difference with 95% confidence interval.

Early therapeutic response (ISI at Week 2).

Measurement variable: ISI total score at Week 2.Analysis metric: Between-group differences in mean change from baseline with 95% confidence intervals.

Durability of insomnia severity (ISI during follow-up).

Measurement variable: ISI total scores at Weeks 6, 8, 10, 12, 14, 16.Analysis metric: Mean change from baseline at each time point; descriptive summaries with between-group estimates.

Sleep quality during follow-up (PSQI).

Measurement variable: PSQI global scores at Weeks 8, 12, 16.Analysis metric: Mean change from baseline; descriptive between-group estimates.

Occurrence and characterization of clinically relevant events.

Measurement variable: Adverse events recorded using validated ADR/AE monitoring checklist (45, 46).Analysis metric: Frequency and proportion by group; descriptive summaries of severity and relatedness.

Behavioral dependency risk.

Measurement variable: Severity of Dependence Scale (SDS) total score (47), assessed through Week 16.Analysis metric: Mean change from baseline to Week 16; between-group estimates with 95% confidence intervals.

Treatment adherence and fidelity.

Measurement variable: Daily Sleep and Treatment Engagement Diary (DSTED) (48).Analysis metric: Percentage adherence and descriptive summaries.

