### Handling missing data & population analysis

4.10

Primary analysis: Intention-to-treat (ITT).Missing data management: Multiple imputation will be used if missing exceeds 10% and a per-protocol analysis will be done alongside ITT analysis to assess robustness.

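### Section 4.2 promises between-group estimates for follow-up ISI and PSQI, but section 4.9.2 gives no between-group contrast or interval for them, only descriptive summaries and within-group graphs

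*Protocol article*

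**What the plan says.** Section 4.2 (Exploratory secondary outcomes) defines durability of insomnia severity by "ISI total scores at Weeks 6, 8, 10, 12, 14, 16", with this metric: "Mean change from baseline at each time point; descriptive summaries with between-group estimates". For PSQI at Weeks 8, 12 and 16 the metric is "Mean change from baseline; descriptive between-group estimates".

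Section 4.9.2 (Exploratory secondary outcome analysis) treats the same data differently: "Follow-up ISI and PSQI scores beyond Week 4 will be summarized descriptively". Results are to appear as mean and SD or median and IQR, and "graphical trends over time will illustrate within-group patterns". It then states: "No formal repeated measures ANOVA or confirmatory longitudinal modeling is planned".

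Two other places bear on the point. The opening of section 4.9 refers back to the outcome definitions: "The exploratory primary and secondary outcomes are defined in detail in the Outcome Measures section". Section 4.10 makes intention-to-treat the primary analysis and says: "Multiple imputation will be used if missing exceeds 10" per cent.

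**The concern.** Section 4.2 says the follow-up data will yield comparisons between arms. Section 4.9.2, which should say how, stops at summaries by arm. This matters for two reasons.

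First, both arms receive the same eight CBT-I sessions, and every woman is selected on a screening ISI between 8 and 21. A trend within one arm therefore mixes the CBT-I effect, regression to the mean and the passage of time. Only the randomised difference between arms at a given visit speaks to whether the effect of the oil procedures persists.

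Second, losses during follow-up may be related to outcome. Under section 3.8 a woman may be withdrawn if she starts drug treatment for insomnia, and under section 4.8.4 a withdrawn woman has no further assessments. If women who sleep badly leave more often from one arm, descriptive summaries could make that arm look better than it is.

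If the contrast is not stated beforehand, it will be chosen after the follow-up data are seen, or readers will have to build it from the tables. Where the tables show medians and IQRs, they cannot readily recover a mean difference with an interval.

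**Working it through.** **Step 1: the text, side by side.**

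| Outcome | Comparison promised in 4.2 | Method given in 4.9.1 or 4.9.2 |
|---|---|---|
| ISI, Week 4 | Difference in mean change, 95% CI | t-test or Mann–Whitney U, effect size with 95% CI |
| ISI, Weeks 6–16 (six visits) | Between-group estimates, no interval mentioned | Summaries and within-group graphs; no contrast |
| PSQI, Weeks 8, 12, 16 (three visits) | Descriptive between-group estimates | Same; no contrast |
| Adverse events | Proportions by group | Chi-square or Fisher's exact test |
| Severity of Dependence Scale | Between-group estimates, 95% CI | Parametric or non-parametric test between groups |
| Adherence | Percentages and descriptive summaries | Parametric or non-parametric test between groups |

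Section 4.9.2 names a comparison between arms for adverse events, dependence and adherence. It names none for the 6 + 3 = 9 durability comparisons. The back-reference in 4.9 confirms the outcome definitions but supplies no method.

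**Step 2: the plan's own figure.** Section 4.5 gives a difference of 4 points (10.9 − 6.9), SD 4.3, two-sided alpha 0.05 and 90% power. The normal formula gives 2 × [4.3 × (1.960 + 1.282) / 4]² = 24.3, so 25 per arm. Using the t distribution, power is 0.897 at 25 and 0.908 at 26, so 26 per arm. Then 26 / 0.85 = 30.6, so 31 per arm. The stated 26 and 31 reproduce and are not in dispute.

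**Step 3: what one follow-up visit could deliver.** The article gives no SD for change scores. Assume SD 4.3 at both time points and a baseline-to-visit correlation ρ between 0.3 and 0.7.

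- Change-score SD = 4.3 × √[2(1 − ρ)] = 5.09, 4.30 and 3.33 at ρ = 0.3, 0.5 and 0.7.
- 95% CI half-width = t(0.975, 2n − 2) × SD × √(2/n).
- With n = 26 per arm the multiplier is 2.009 × 0.277 = 0.557, giving 2.83, 2.40 and 1.86 ISI points.
- With n = 31 per arm the multiplier is 2.000 × 0.254 = 0.508, giving 2.59, 2.18 and 1.69.
- With baseline adjustment the residual SD is 4.3 × √(1 − ρ²) = 4.10, 3.72 and 3.07. At n = 26, using the same multiplier as an approximation, the half-widths are about 2.3, 2.1 and 1.7.

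So a difference at a single visit, which needs no longitudinal model, can be estimated with useful precision relative to the 4 points assumed for Week 4.

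**Step 4: how large a mixed model would be.** Section 4.2 gives eight post-baseline ISI visits (Weeks 2, 4, 6, 8, 10, 12, 14 and 16). An unstructured covariance then has 8 × 9 / 2 = 36 parameters for 62 women. Table 1 omits Week 10; with seven visits the count is 7 × 8 / 2 = 28. PSQI has four post-baseline visits, hence 4 × 5 / 2 = 10.

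**The case against.** The strongest defence is that the two sections can be read together. Section 4.2 stands, section 4.9 points to it, and a difference in mean change at each visit needs no longitudinal model. Section 4.2 attaches 95% intervals to Weeks 2 and 4 but not to follow-up ISI and PSQI, so the lighter treatment looks deliberate. Every outcome is declared exploratory, and forgoing formal modelling of secondary follow-up data is a legitimate choice. Section 8 says that a full protocol and SAP exist, and the detail may be there.

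Much of this stands, and it rules out three stronger readings that a reader might infer:

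- **That every longitudinal model is excluded.** The sentence excludes a formal repeated-measures ANOVA and confirmatory modelling. An exploratory mixed model is unplanned, not barred.
- **That durability will not be estimated at all.** Section 4.2 still commits to between-group estimates. The reference to within-group patterns describes the graphs only.
- **That the summaries must rest only on women present at each visit.** Section 4.10 does not confine multiple imputation to Week 4. If the anticipated 15% attrition occurred, the 10% trigger would be passed. What 4.10 leaves open is whether the threshold is applied visit by visit.

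Nor is there a multiplicity problem to count here, since 4.9.2 schedules no significance tests of follow-up ISI.

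The mismatch itself does not go away. The article's own analysis section gives methods for other secondary outcomes and omits these, so condensation alone does not explain the gap. An exploratory, estimation-focused trial also has particular reason to show an estimate with its uncertainty.

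**Conclusion.** The point holds in a limited form. Sections 4.2 and 4.9.2 do not match: nine durability comparisons are promised between arms, and the analysis section gives none of them a contrast or interval. The descriptive output it does specify cannot separate persistence of the add-on difference from what both arms share.

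The consequence is modest. These are secondary, exploratory outcomes, and the Week 4 primary analysis is unaffected. No figure in the plan is wrong. The half-width of about 2.4 ISI points at one visit (1.9 to 2.8 across the assumed correlations, 26 per arm, no baseline adjustment) shows what the collected data could provide; it does not measure an error. It assumes that the pilot SD of 4.3 applies at baseline and at follow-up. That follow-up loss depends on outcome is a possibility created by sections 3.8 and 4.8.4, not something the documents establish.

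**What to change.** Align section 4.9.2 with section 4.2. State that, for ISI at each visit after Week 4 and for PSQI at Weeks 8, 12 and 16, the baseline-adjusted difference between arms will be reported with a 95% CI and labelled exploratory.

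Preferably, obtain these from one mixed model per instrument with arm, visit, arm-by-visit interaction and baseline score, fitted to all post-baseline visits. Under a missing-at-random assumption this uses the earlier scores of women who later drop out. Name a parsimonious covariance fallback in advance, because an unstructured matrix may be too large for 62 women. Separate baseline-adjusted regressions at each visit are an acceptable minimum.

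An average over Weeks 6 to 16 may be added but should not replace the visit-specific differences, because it can hide waning, which is the durability question. The Week 4 primary analysis in section 4.9.1 stays as written. While editing, reconcile the ISI visit list in section 4.2 with Table 1 on Week 10, and say in section 4.10 whether the 10% threshold applies per visit.

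The cost is a few sentences and one model per instrument, with no new data. The price is a covariance assumption at this sample size and, for the mixed model, reliance on missing at random.

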## Conclusion

7

This exploratory randomized controlled trial evaluates the feasibility, safety, adherence, and preliminary signal estimation associated with integrating *Siro-pichu* and *Padabhyanga* with CBT-I for perimenopausal insomnia. The study is not designed to determine causality or establish efficacy. Findings will be interpreted within a hypothesis-generating framework and are intended to guide the design of future larger, multi-center, adequately powered confirmatory trials.

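### Safety is a declared aim of an estimation-focused plan, yet the between-arm adverse event comparison is a Chi-square or Fisher test with no risk difference, interval or zero-event bound

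*Protocol article*

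**What the plan says.** Section 4.9.2 (Exploratory secondary outcome analysis) sets the adverse event analysis: "Adverse events will be summarized by frequency and proportion in each group. Between-group comparisons will be explored using Chi-square or" Fisher's exact tests. It closes by calling the findings exploratory.

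Section 4.2 (Exploratory secondary outcomes) gives the metric for adverse events as "Frequency and proportion by group; descriptive summaries of severity and relatedness". In the same list, Week 4 PSQI, Week 2 ISI and the Severity of Dependence Scale each receive a between-group estimate with a 95% confidence interval, as Week 4 ISI does in section 4.1. Follow-up ISI and PSQI receive between-group estimates without a stated interval. Adverse events receive neither an estimate nor an interval.

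On the purpose of the analyses, section 4.9 says: "Analyses are estimation-focused and hypothesis-generating in nature". Section 4 says the same of all outcomes. Section 7 (Conclusion) says the trial "evaluates the feasibility, safety, adherence, and preliminary signal estimation" of the combined treatment, so safety is one of its declared aims.

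On size, section 4.5 states that "the final planned sample size was set at 31 participants per arm". This comes from a calculation on the ISI alone; no calculation concerns adverse events.

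**The concern.** A significance test and an estimate with an interval answer different questions. The test asks whether the two arms are distinguishable at the 5% level. The interval shows which excesses of harm remain compatible with the data. A small trial meant to inform later ones needs the second answer, and the plan asks for it in general terms but names only the first for adverse events.

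The dependence scale, which section 6 says is not validated for non-pharmacological procedures, is given a 95% interval, while adverse events, the direct measure of harm, are not. If the test is the headline comparison, a non-significant result may be all that a later planner takes away, even where the counts are compatible with a sizeable excess in the add-on arm.

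**Working it through.** **1. The plan's own size (section 4.5).** Inputs: difference 4 points, SD 4.3, two-sided alpha 0.05, power 90%, attrition 15%.

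- Normal formula: n = 2 × 4.3² × (1.960 + 1.282)² / 4² = 24.3, so 25 per arm.
- t-test solution: 25.3, so 26 per arm, which is the plan's figure.
- Attrition: 26 / 0.85 = 30.6, so 31 per arm, again the plan's figure.

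The size is reproduced. It was set for the ISI and gives no assurance about adverse events.

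**2. Power of the named tests.** The documents state no adverse event rates, so every rate below is an assumption. Exact power = Σ over (a, b) of Bin(a; n, p₁) × Bin(b; n, p₀) × 1[p-value(a, b) < 0.05], with n per arm, p₀ the control rate and p₁ the add-on rate. Chi-square is without continuity correction.

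| Control v add-on | Excess (points) | Fisher, n = 31 | Chi-square, n = 31 | Fisher, n = 26 | Chi-square, n = 26 |
|---|---|---|---|---|---|
| 5% v 15% | 10 | 10% | 27% | 8% | 22% |
| 10% v 20% | 10 | 10% | 20% | 9% | 18% |
| 5% v 20% | 15 | 26% | 47% | 22% | 40% |
| 10% v 25% | 15 | 23% | 35% | 19% | 31% |
| 5% v 25% | 20 | 46% | 65% | 40% | 57% |
| 10% v 30% | 20 | 39% | 52% | 32% | 47% |
| 5% v 30% | 25 | 66% | 79% | 58% | 73% |
| 10% v 35% | 25 | 57% | 68% | 47% | 62% |

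For a harm that cannot occur in the control arm (p₀ = 0), power is one binomial tail. At 31 per arm, Fisher needs at least 6 events against 0, and uncorrected Chi-square needs at least 4.

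- 0% v 10%: P(X ≥ 6) = 8%; P(X ≥ 4) = 38%.
- 0% v 15%: P(X ≥ 6) = 32%; P(X ≥ 4) = 70%.
- 0% v 20%: P(X ≥ 6) = 61%; P(X ≥ 4) = 89%.

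**3. What an interval would add: 5/31 v 0/31.**

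- Fisher, two-sided: 2 × C(31,5) / C(62,5) = 2 × 169,911 / 6,471,002 = 0.053.
- Wilson 95% limits: 5/31 = 0.161 (0.071 to 0.326); 0/31 = 0 (0 to 0.110).
- Newcombe lower limit: 0.161 − √[(0.161 − 0.071)² + 0.110²] = +0.019.
- Newcombe upper limit: 0.161 + √[(0.326 − 0.161)² + 0²] = +0.326.

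The difference is +16 points, interval about +2 to +33, beside a Fisher p-value just above 0.05.

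Two more cases at 31 per arm:

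- 5 v 1: Fisher p = 0.195; difference +12.9 points (−2.9 to +29.6).
- 2 v 2: p = 1.0; interval −15 to +15 points.

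**4. No events in an arm.** Exact two-sided 95% upper limit = 1 − 0.025^(1/n): 11.2% at n = 31 and 13.2% at n = 26.

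**The case against.** The strongest reply is that nothing in the protocol draws a safety conclusion from the test. The comparison is described as exploratory, confirmatory power is disclaimed in sections 4.5 and 6, and there is no harm margin or safety decision rule. This stands. A reader might infer that a non-significant test is going to be presented as proof of safety; the documents do not say so.

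A reader might also infer that the p-value is the only comparative safety information. It is not. Proportions per arm will be reported, severity and relatedness will be summarised, and each event is assessed individually (sections 4.4.2 and 4.14). If the counts are of participants with an event, anyone can compute the interval from them.

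Nor is the test nearly always non-significant. With 5% or 10% in controls, an excess of 25 points at 31 per arm is more likely than not to be detected by either test, and 0% v 20% has 61% power with Fisher and 89% with Chi-square. The documents do not say that the expected harms are rare, and they put no figure on a relevant excess.

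Finally, the article condenses a fuller plan available on request (section 8), and interval methods often sit there. This carries some weight for the choice of method. It does not remove the point, because the article does state how adverse events will be compared, and it names intervals for other outcomes in the same list.

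**Conclusion.** The point holds as a mismatch between the stated framework and the stated method: an estimation-focused plan with safety among its aims compares adverse events between arms by a test and names no effect estimate, interval or zero-event bound.

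The test is weakly informative at this size. With control rates of 5% or 10%, power at 31 per arm is below 50% with either test for excesses up to about 15 points, and below 50% with Fisher at 20 points. With no events expected in controls, Chi-square does better (70% for 0% v 15%) and Fisher does not (32%). All of this rests on assumed rates, on counting participants with at least one event, and on Chi-square without continuity correction. The interval for 5/31 v 0/31 and the upper limit for 0/31 need no assumed rate, only those counts.

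The severity is minor. The documents do not support the stronger claim that the trial's safety conclusion is unsound, since they plan no such conclusion from the test.

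**What to change.** In sections 4.2 and 4.9.2:

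- Report, per arm, the proportion of participants with at least one adverse event, with an exact 95% confidence interval.
- Make the between-group risk difference with a 95% Newcombe (or exact) interval the main comparative safety result. Any Chi-square or Fisher p-value is then descriptive only.
- Where an arm has no events, give the exact upper limit.
- State that a non-significant difference will not be reported as evidence of equal safety.

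The cost is a change of wording and a few lines of analysis code. The safety statement becomes less favourable: with no events in 31 participants, for example, it would have to say that rates up to about 11% are not excluded. Sample size, data collection and the primary analysis stay as they are.
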